### Economic analysis

Economic evaluation will be carried out in the form of an incremental cost-effectiveness analysis over the 12-month trial period, from a NHS and personal and social service perspective [18]. Intervention costs will be recorded by the research team and include delivery costs within the trial, supervision costs and appropriate capital costs. Resource use in physical units will be collected using an adapted Health Economic/Service Utilisation Questionnaire and case notes. Resource units will be valued by multiplying quantities by the corresponding market prices or national average unit costs.

Health-related quality of life will be measured using the EuroQol 5 dimensions, 5 levels (EQ-5D-5 L) questionnaire [19]. Health utilities are converted into quality-adjusted life years (QALYs), by calculating the area under curve [20]. An incremental cost-effectiveness ratio (ICER) will be calculated by combining difference in costs between groups and difference in QALYs between groups and compared with the national willingness-to-pay threshold to determine cost-effectiveness.

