**Methods/design:**

SCIMITAR+ is a multicentre, pragmatic, two-arm, parallel-group, individually randomised controlled trial.

We aim to recruit 400 participants aged 18 years and above with a documented diagnosis of bipolar disorder, schizophrenia or schizoaffective disorder who smoke. Potentially eligible participants identified in primary or secondary care will be screened, and baseline data collected. Eligible, consenting participants will be randomly allocated to one of two groups. In the intervention arm, the participant will be assigned a mental health professional trained to deliver smoking-cessation interventions who will work with the participant and participant’s GP or mental health specialist to provide an individually tailored smoking-cessation service. The comparator arm will be usual care – following current NICE guidelines for smoking cessation, in line with general guidance that is offered to all smokers, with no specific adaptation or enhancement in relation to severe mental ill health.

The primary outcome will be self-reported smoking cessation at 12 months verified by expired carbon monoxide (CO) measurement. Secondary outcome measures include Body Mass Index at 12 months, the Fagerström Test for Nicotine Dependence, Motivation to Quit questionnaire, SF-12, PHQ-9, GAD-7, EQ-5D-5 L, and health service utilisation at 6 and 12 months. The economic evaluation at 12 months will be conducted in the form of an incremental cost-effectiveness analysis.

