## Background

The physical health of people with severe mental ill health (SMI), such as schizophrenia and bipolar disorder, is often poor with people with a diagnosis of schizophrenia reported to die 20–25 years earlier than those in the general population [1]. One of the largest contributory factors to this early mortality is smoking [2]. Smoking is a preventable health hazard, with proven associations with diseases such as cancer and heart disease. A recent study compared outcomes for people with SMI who smoke to people with SMI who do not smoke and found that on average people with SMI who smoke die nearly 10 years earlier than those who do not smoke [3]. Smoking is, therefore, one of the most important modifiable risk factors for this excess mortality, though smoking may be only one of several reasons for this observed difference. However, whilst the number of people in the general population who smoke has been steadily declining over recent decades [4], the number of people with SMI who smoke has not been declining at the same rate. People with SMI are still more likely to smoke [5] and to smoke more heavily, extracting more nicotine from each cigarette, than those in the general population [6].

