### Research objectives

To establish the clinical effectiveness of a bespoke smoking-cessation intervention compared with usual care for people with severe mental ill health.To establish the cost-effectiveness of a bespoke smoking-cessation intervention for people with severe mental ill health.

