### Outcome measures

Data will be collected from participants at baseline and at 6 and 12 months post randomisation. Baseline and follow-up assessments will take place during face-to-face meetings with the participant in order to measure height and weight to calculate the Body Mass Index (BMI), and to take CO readings. As face-to-face follow-up is preferred every effort will be made to collect, as a minimum, a reduced set of data by this method. Where it is not possible to meet with the participant for face-to-face follow-up data collection, the participant will be offered the option of completing the questionnaires by telephone or have the questionnaires sent to them by post for them to complete and return. If it is not possible to make contact with the participant for follow-up, a family member or friend named by the participant at their baseline interview as a person who could be contacted, will be asked to verify the participant’s smoking status.

The primary outcome measure will be cessation of smoking at 12 months assessed according to the Russell standard. Smoking cessation will be defined as having an expired-air CO measurement of less than 10 ppm *and* self-reporting as a quitter (responding ‘not even a puff’ to the question ‘Have you smoked in the last week?’).

Secondary outcomes at 6 and 12 months post randomisation will include measures of smoking status, general mental health functioning, BMI, health-related quality of life, health service use, and adherence with smoking-cessation advice from MH-SCP (Table 1). The flow of participants through the trial is shown in Fig. 2.

**Table 1 Tab1:** Outcome measure and collection time point

Assessment	Time point (months post randomisation)		
	Baseline	6	12
Eligibility and consent			
Eligibility	X		
Consent	X		
Background and follow-up			
Personal details, general health	X		
Body Mass Index	X	X	X
Mental health details			
Mental health history	X		
Current mental health status	X	X	X
Current medications	X	X	X
Referrals to mental health services		X	X
Admissions to hospital related to mental health		X	X
Smoking details			
Smoking history	X		
Current smoking status	X	X	X
Use of electronic cigarettes	X	X	X
Use of smoking-cessation services	X	X	X
CO measurement	X	X	X
Adverse event reporting	Ongoing collection		
Questionnaires			
Fagerström Test for Nicotine Dependence (FTND) [17]	X	X	X
Motivation to Quit questionnaire (MTQ)	X	X	X
Patient Health Questionnaire (PHQ-9)	X	X	X

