### Sample size

The SCIMITAR+ trial has been powered to detect a relative increase in quitting of 1.7 (baseline quit rate 20%, intervention quit rate 34%) using a two-sided significance level of 5% at 80% power. This would require a sample size of 314 participants using equal (1:1) randomisation. Allowing for a 20% loss to follow-up would give a total sample size of at least 393. We therefore propose to recruit 400 participants in total to ensure sufficient power.

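### The Economic analysis lets a 12-month cost per QALY determine cost-effectiveness without limiting the verdict to 12 months, although the survival benefit the protocol cites lies beyond that window

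*Protocol article*

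**What the plan says.** The Economic analysis section of the protocol article plans an "incremental cost-effectiveness analysis over the 12-month trial period", from an NHS and personal social services perspective. On effects it says: "Health utilities are converted into quality-adjusted life years (QALYs), by calculating the area under curve", using the EQ-5D-5L. The ICER is then "compared with the national willingness-to-pay threshold to determine cost-effectiveness". The abstract repeats the horizon: "The economic evaluation at 12 months will be conducted in the form of an incremental cost-effectiveness analysis".

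The objective this serves, in Research objectives, has no time limit: "To establish the cost-effectiveness of a bespoke smoking-cessation intervention for people with severe mental ill health".

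The Background reports a study finding that "on average people with SMI who smoke die nearly 10 years earlier than those who do not smoke", and adds that smoking may not be the only cause of that gap. The Discussion again presents smoking as a modifiable risk factor for shortened life. On timing, Outcome measures states: "Data will be collected from participants at baseline and at 6 and 12 months post randomisation". The Sample size section targets quit rates of 20% and 34%. The article gives no unit cost, expected utility gain, expected cost difference or threshold value.

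**The concern.** The rule sets the cost of the service against only the first year of its health effect. The eight to 12 offered sessions, their supervision and the capital costs are counted within the trial period. The added survival that motivates quitting comes years later and contributes essentially nothing to a 12-month QALY.

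The measurement schedule shrinks the 12-month effect further. The primary outcome needs abstinence only in the week before month 12, several sessions may precede a quit date, and repeated attempts are expected. Someone who quits late is a full clinical success but adds little area under a utility curve measured at 0, 6 and 12 months.

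At stake is what the trial may conclude. A ratio above the threshold could be reported as showing that the service is not cost-effective, when it shows only that the service did not pay for itself in QALYs within a year. A ratio below the threshold could owe more to unrelated service use than to quitting.

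**Working it through.** **The plan's own figures.** For 20% against 34% (two-sided 5%, 80% power, pooled variance, no continuity correction):
- n per arm = [1.960 × √(2 × 0.27 × 0.73) + 0.842 × √(0.20 × 0.80 + 0.34 × 0.66)]² / 0.14² = 156.7, so 157 per arm and 314 in total.
- 314 / 0.8 = 392.5, so 393.

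Both agree with the article. The target risk difference is 0.34 − 0.20 = 0.14. With 400 recruited and 20% lost, 400 × 0.8 / 2 = 160 per arm are analysed.

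**Time credited to a utility gain g** (linear area under the curve, measured at 0, 0.5 and 1 year):
- seen only at month 12: 0.5 × g/2 = 0.25g
- present from month 6: 0.5 × g/2 + 0.5 × g = 0.75g
- present from day 0 (ceiling): 1.0g

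**12-month QALY gain per participant** = 0.14 × g × time weight. Assumption, not in the article: g = 0.01 to 0.10 per extra quitter, and no gain in anyone else.

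| Gain present from | g = 0.01 | g = 0.10 |
|---|---|---|
| month 12 | 0.00035 | 0.0035 |
| month 6 | 0.00105 | 0.0105 |
| day 0 | 0.0014 | 0.014 |

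**Precision.** SE of the QALY difference = SD × √(2/160). Assumed SD 0.15 gives 0.017; SD 0.25 gives 0.028. The largest gain in the table is 0.014/0.017 ≈ 0.8 to 0.014/0.028 = 0.5 standard errors. For quitting, SE = √[(0.16 + 0.2244)/160] = 0.049, and 0.14/0.049 ≈ 2.9 standard errors. The trial can resolve its target effect on quitting, but not the 12-month QALY that follows from it.

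**Can the verdict be predicted?** Assume a threshold of 20,000 to 30,000 pounds per QALY.
- Highest net cost that passes: 0.00035 × 20,000 = 7 pounds to 0.0105 × 30,000 = 315 pounds; ceiling 0.014 × 30,000 = 420 pounds.
- Delivery cost at an assumed 20 to 60 pounds per session: 8 × 20 = 160 to 12 × 60 = 720 pounds. Net cost may differ, since usual care and other service use also count.
- The ranges overlap. A net cost of 300 with 0.005 QALY gives 60,000 per QALY (fails); 100 with 0.0105 gives about 9,500 (passes).
- Let ΔQ and ΔC be the true QALY and cost differences and λ the threshold. The chance that the point estimate fails is Φ(−(λΔQ − ΔC)/SE), with SE = √(2/160) × √((λ·SD_Q)² + SD_C²), treating costs and QALYs as independent. With ΔQ 0.001 to 0.014, ΔC 100 to 700 pounds, and (SD_Q, SD_C) of (0.15, 2,000) or (0.20, 5,000), it runs from about 0.3 to 0.95 and is above 0.5 in most scenarios.

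**What lies outside the window (illustration only).** Life-years per participant = 0.14 × 10 × share of the gap regained × (1 − later relapse). A cautious case takes 10% regained and 50% relapse: 0.14 × 10 × 0.1 × 0.5 = 0.07 life-years. Valued at utility 0.7 and discounted at 3.5% from 30 years ahead, this is 0.07 × 0.7 × about 0.35 ≈ 0.017 QALY, already above the 12-month ceiling of 0.014. Less cautious inputs give more.

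**The case against.** The strongest reply is that this is a condensed article. Extrapolation models, cost per quitter and uncertainty analysis normally sit in the full protocol or a health economics plan, neither of which is shown. Their absence here is no fault, and a longer-horizon model may exist. That stands. The point is therefore confined to the rule the article does state: the 12-month ratio against the threshold determines cost-effectiveness, with no qualifier.

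Second, the horizon is disclosed twice, and a within-trial analysis is a legitimate primary analysis. Both are true. But disclosing the horizon of the analysis does not limit the conclusion, and the objective has no time limit.

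Third, a reader might infer that an intervention meeting its clinical target is likely to be declared not cost-effective. The document does not support this. Apart from the 14-point difference and the number of sessions, every input to such a forecast is assumed. Usual care also has costs, other service use could offset or add to them, and participants who do not quit may also change in utility, which the table sets to zero. Failure is the more frequent result under the inputs tried, but it reverses at low net cost.

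Fourth, the whole 10-year gap cannot be credited to quitting. The Background says smoking may be only one of several reasons for it, and relapse after month 12 is unknown. So the lifetime calculation supports a direction, not a multiple.

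**Conclusion.** The point holds in limited form. As a measure of the first year, the 12-month ratio is sound. As an unqualified verdict it is biased against the intervention, because it counts delivery costs and leaves out the survival benefit the protocol itself cites. It cannot alone settle the second objective.

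The size of the bias and the direction of the 12-month verdict cannot be derived from the article. If utility gains accrue only to the extra quitters (up to 0.10 each), with QALY SD 0.15 to 0.25 and 160 per arm, the 12-month gain (at most about 0.014) is smaller than its standard error (0.017 to 0.028). Chance and other service use could then drive the result either way. The primary outcome, sample size and data collection are unaffected. The change is worth making because it alters what the trial may conclude.

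**What to change.** In the Economic analysis section:

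1. Label the 12-month ICER a within-trial result, and limit the threshold conclusion to cost-effectiveness over 12 months.
2. Add the incremental cost per additional CO-verified quitter at 12 months, with its uncertainty. This brings the primary outcome into the economic result. The article names no threshold for this measure, so it informs the verdict but does not decide it.
3. Make any general statement on cost-effectiveness depend on a longer-horizon scenario driven by 12-month quit status, with relapse, discounting, QALYs per quitter and later costs stated in advance and varied. If such a model already exists in the full protocol or a health economics plan, a reference to it is enough.

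Item 1 is wording. Item 2 is a few lines of analysis on data already collected. Item 3 is a modest desk exercise whose drawback is reliance on outside assumptions, so its results should be given as a range. No new participants or measurements are needed.

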## Discussion

People with SMI experience significant health inequalities and one of the most important modifiable risk factors for reduced life expectancy is smoking. It is, therefore, important to develop evidence-based interventions to help people with SMI to quit smoking. The SCIMITAR+ trial is the largest trial to our knowledge to investigate the clinical effectiveness and cost-effectiveness of a bespoke smoking-cessation service for people with severe mental ill health.

### Study status

Recruitment to the SCIMITAR+ trial began in October 2015 and results are expected in 2018.

## Abbreviations

BMI: Body Mass Index
CMHT: Community Mental Health Team
CO: Carbon monoxide
DSM: *Diagnostic and Statistical Manual of Mental Disorders*
EQ-5D-5L: EuroQol 5 dimensions, 5 levels questionnaire
GAD: General anxiety disorder
GP: General practitioner
ICD: *International Classification of Diseases*
MH-SCP: Mental health smoking-cessation practitioner
NICE: National Institute of health and Care Excellence
NRT: Nicotine replacement therapy
PHQ: Patient Health Questionnaire
SCIMITAR: Smoking Cessation Intervention for severe Mental Ill health Trial
SF-12: 12-item Short Form Health Survey
SMI: Severe mental ill health
